### Participant Recruitment

All eligible pregnant women who smoke and live in Tasmania (Australia) are invited to participate in the study. Statewide recruitment is facilitated by drawing on data from the Tasmanian Health Service’s digital medical record (DMR) and encompasses multiple strategies to maximize reach. A research midwife, with access to the Tasmanian Health Service’s DMR, conducts “cold calling” of all women who self-reported smoking in the last 7 days during their initial antenatal “booking in” appointment (usually around 10 weeks gestation). Using information stored on the DMR, the midwife pre-screens women for eligibility (eg, self-report smoking, 16 years or older) and telephones them to invite them to participate in the study. With their verbal consent, the details of interested women are recorded and forwarded to the research team.

Antenatal staff of the Tasmanian Health Service (including physicians and midwives) provide study information (in the form of a flyer) to eligible participants during antenatal appointments. With their consent, the contact details of interested women are forwarded to the research team. In addition, the study is advertised through flyers placed in general practitioner (GP) clinics, outreach centers and community hubs across Tasmania. Informal advertising via social media (eg, Facebook) and television and radio interview exposure may also be utilized. Consequently, potential participants could also self-refer to the study by contacting the researchers directly.

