### Eligibility Criteria

Women who express interest in participating in the study (either self-refer or consent to a health professional forwarding their contact details to research staff) are contacted by research staff and screened for eligibility using a previously validated protocol [24]. To be eligible for study entry, women must be (1) pregnant (20 weeks gestation or less); (2) at least 16 years of age; (3) self-report as being a current smoker (“even a single puff in the last 7 days”); (4) attending routine antenatal care provided by the Tasmania Health Service or participating GP center (Tasmanian, Australia); and (5) be able to attend a minimum of 3 appointments at 1 of the 3 data collection sites across Tasmania (Launceston General Hospital, Royal Hobart Hospital, or Mersey Community Hospital). Women younger than 18 years (but 16 years or older) require the consent of their parent, guardian, or senior antenatal health provider to participate in the study.

Potential participants are excluded from study entry if they self-report as non-smoking (ie, “have not smoked, even a single puff in last 7 days”) or if they have a cognitive or intellectual impairment that will inhibit fulfillment of participation requirements (eg, completion of surveys and/or attend organized study appointments). Participants who are found to be “gaming” (eg, those who tell researchers they are pregnant and/or smoking untruthfully to enroll in study) are also excluded from further participation and their data discarded. All participants are asked to nominate and are encouraged to bring along to study visits a support person, preferably a person they co-habit with (eg, spouse, father of child, or family member).

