### Assignment of Interventions

Participants are assigned to the same group (either control or the treatment group) for 3 consecutive months (interchangeably for 18 months), such that participants recruited in the first 3 months are allocated to the control group and participants recruited in the following 3 months are allocated to the treatment group. This design was chosen to assist participant blinding to group allocation, given the heightened potential for the women recruited to know each other and/or discuss research participation. Since participants in this study are recruited following their first antenatal appointment, participants recruited around the same time will have similar due dates. As membership to parents’ groups and hospital-run parentcraft classes is usually assigned by due date/gestation, and due to the relatively small recruitment pool (Tasmania has a population of 515,000 and only 3 tertiary hospitals), adopting a fully randomized, parallel group controlled design would likely jeopardize participant allocation concealment (ie, differing incentive amounts), thus introducing bias (eg, recruited women declining/delaying enrolment due to allocation, participants not being as motivated to quit smoking due to lesser incentive amount). As well as assigning participants to the same group in 3-month intervals, participants who report knowing another participants or are recruited by another participant are assigned to the same group.

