#### 12-Month Telephone Call and Visit

Each participant, regardless of smoking status, is contacted via telephone 12 months after the delivery of their baby. The 12-Month Follow-Up Questionnaire is administered via telephone and participants are asked their current smoking status. Participants who self-report abstinence (7-day point prevalence) during this call are invited to verify smoking abstinence via a CO breath sample in a follow-up visit and be offered an AUD$10 shopping voucher (regardless of verification status) to thank them for their participation. This marks the completion of their participation in the study.

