Participants, regardless of group allocation, will be regrouped to either PIQ-POS or PIQ-NEG, as determined by the ratio of positive compared to negative support they report receiving from their support partners. The abstinence rates of these regrouped PIQ-POS and PIQ-NEG participants will then be compared at 3 time points; end-of-pregnancy, end-of-study (2 months postpartum), and 12 months postpartum.

#### Hypothesis 4

The fourth hypothesis (H4) is providing incentives for pregnant smokers to quit is more effective than “usual care” antenatal smoking cessation support at promoting smoking cessation.

The quit rates of participating women will be compared to the average quit rate of a historical control of women receiving antenatal care by the Tasmanian Health Service from 2011 to 2015 [34].

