## Results

The recruitment phase of the study has concluded and postpartum data collection is ongoing. Data collection is anticipated to be complete by late 2017. Outcomes of the trial will be published within a year (12 months) of completing final 12-month follow-up data collection. The study results will be disseminated via conference presentations and papers published in academic peer-reviewed journals. The participants, healthcare professionals, and public will be informed of the study results through email correspondence and local media.

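### The 2011 to 2015 comparator for Hypothesis 4 appears to run into the trial's own recruitment period and can contain its incentivised participants

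*Protocol article*

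**What the plan says.** Under Planned Analyses, Hypothesis 4 sets incentives against usual antenatal cessation support. The quit rates of participating women are to be compared with the average quit rate of a "historical control of women receiving antenatal care by the Tasmanian Health Service from 2011 to 2015". This addresses the third aim listed under Objectives.

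Participants come from the same service. Under Participant Recruitment, a research midwife uses its digital medical record to telephone women statewide who reported smoking at their booking appointment, "usually around 10 weeks gestation". Eligibility Criteria require antenatal care from that service or a participating GP center, and a gestation of no more than 20 weeks.

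The timing is spread over several sections. Assignment of Interventions alternates the two groups in three-month blocks, "interchangeably for 18 months". The 12-Month Telephone Call and Visit section says each woman "is contacted via telephone 12 months after the delivery of their baby". Results states: "The recruitment phase of the study has concluded and postpartum data collection is ongoing", and then: "Data collection is anticipated to be complete by late 2017". The article gives no date of first or last enrolment, and does not say that enrolled women or the recruitment period are left out of the comparator.

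**The concern.** A historical control represents care before the programme under test. That requires its window to close before the first woman is offered the intervention, or enrolled women to be taken out. The window here reaches 2015, and the article's timeline places the start of recruitment no later than early 2015.

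Two things follow if enrolled women are in the comparator. Some women count on both sides of the contrast, so the groups are not independent. The rate labelled usual care also includes women who were paid to quit, which, if incentives work, raises it and shrinks the difference that Hypothesis 4 is meant to show.

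**Working it through.** The article states no start date, so there is no figure to reproduce. The start can only be worked back from the stated end.

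**Inputs**
- Accrual: 18 months (Assignment of Interventions).
- Gestation at entry: at most 20 weeks (Eligibility Criteria); booking is usually at about 10 weeks (Participant Recruitment).
- Last contact: 12 months after delivery (12-Month Telephone Call and Visit).
- End of data collection: late 2017 (Results). I take 31 December 2017, which gives the latest possible start.
- Delivery at 40 weeks: my assumption.

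**Implied first enrolment**

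Minimum span = accrual + (delivery gestation − entry gestation) + 12 months = 18 + 4.6 (20 weeks) + 12 = 34.6 months.

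- Last enrolment: 31 December 2017 − 365 days − 140 days = 13 August 2016.
- First enrolment: 13 August 2016 − 548 days (18 months) = 12 February 2015.

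**Sensitivity, 18 months of accrual**

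| Close | Entry (weeks) | Delivery (weeks) | Latest start | Months from start to 31 Dec 2015 |
|---|---|---|---|---|
| 31 Dec 2017 | 20 | 40 | 12 Feb 2015 | 10.6 |
| 31 Dec 2017 | 20 | 37 | 5 Mar 2015 | 9.9 |
| 31 Dec 2017 | 10 | 40 | 4 Dec 2014 | 12.9 |
| 30 Sep 2017 | 20 | 40 | 12 Nov 2014 | 13.6 |

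**Overlap with a window ending 31 December 2015**
- By enrolment date: 12 February to 31 December 2015 is 322 days; 322 / 30.4375 = 10.6 months.
- By delivery date: the last delivery must fall by 31 December 2016. If all women enter at the same gestation, the first delivery is 18 months earlier, about 2 July 2015. That leaves 182 days, or 6.0 months.
- By smoking status at about 8 months' gestation, when the End-of-Pregnancy Visit takes place: about 7 months.
- If the first woman entered on 12 February 2015 at 10 weeks but the last entered at 20 weeks, the first delivery is 210 days after entry, about 10 September 2015. That leaves 112 days, or 3.7 months, by delivery date.

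**If accrual was shorter than stated**
- By enrolment date, overlap disappears only if accrual is at most (730 − 140) / 30.4375 − 12 = 7.4 months. Twelve months of accrual still implies a start by mid-August 2015, and nine months by mid-November 2015.
- By delivery date, with a common entry gestation, overlap disappears if accrual is 12 months or less.

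**Illustrative size of the bias**

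The comparator's size is not given, so I assume 1,000 to 5,000 smokers. The planned 108 women spread evenly over 18 months is 6 per month. This puts about 36 (6 × 6.0) to 63 (6 × 10.6) women in the overlap, or 36/5,000 = 0.7% to 63/1,000 = 6.3% of the comparator. The article cites 32% against 9% from the earlier incentive study, a gap of 23 points. At that effect the comparator rate would rise by 0.007 × 23 = 0.2 to 0.063 × 23 = 1.4 points.

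**The case against.** The strongest reply is that the overlap is possible but not shown. The comparator is an average rate from a cited source that is not available here. That source may stop before the end of 2015. A mid-2015 cut-off leaves about 4.5 months by enrolment date and essentially nothing by delivery date, and a cut-off at the start of 2015 removes the overlap for a February start. It may already exclude trial women, and participants enrolled through GP centers may fall outside it. Late 2017 is also only an anticipated date. All of this stands, and it limits the point to what the window permits as written. On the date, the article does promise publication within 12 months of the final 12-month follow-up and expects results by the end of 2018, which fits follow-up ending in about late 2017.

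It is also fair to say that the effect is small and conservative. It works against Hypothesis 4, so it would not by itself produce a false claim of benefit. The study is powered on Hypothesis 1, and Hypotheses 1 to 3 do not use this comparator.

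A reader might go further in three ways that the article does not support.
- That the passages contradict one another. They do not: a start by February 2015 satisfies every stated duration and date.
- That 12-month outcomes for Hypothesis 2 would be lost. That needs recruitment to start after 2015, which the article nowhere says. It plans to contact every woman at 12 months and ties publication to the end of that follow-up, so the completion date needs no rewording.
- That at least 10.6 of 60 months, about 18% of the comparator, is contaminated. The 10.6 months is not a minimum, since counting by delivery gives about 6 or fewer, and a share of calendar months is not a share of women.

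**Conclusion.** The point holds as a weakness in how the Hypothesis 4 comparator is defined. With delivery at 40 weeks and a close on 31 December 2017, the stated timeline puts first enrolment no later than about February 2015. A 2011 to 2015 window in the same statewide service then extends into recruitment by about 10.6 months by enrolment date or about 6 months by delivery date, provided it runs to the end of 2015. Trial women can therefore be counted as usual care; that they actually are is not established.

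Any bias would be toward no difference and is probably small: 0.2 to 1.4 points on an assumed comparator of 1,000 to 5,000 smokers. It bears on the third stated aim only. It still deserves correction, because a comparator meant to represent usual care should not include women who received the intervention.

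**What to change.** In Hypothesis 4, end the comparator window before the date of first enrolment, or keep the window and remove enrolled women from it. One sentence in the analysis plan and a re-cut of the comparator data would do it. The article describes data collection as ongoing, so the change can be made before the final analysis.

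The cost of the first option is a slightly shorter comparator period. With a start in February 2015, 2011 to 2014 remains in full. The second option keeps the whole period but needs enrolled women to be identifiable in the comparator records.

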## Results

The recruitment phase of the study has concluded and postpartum data collection is ongoing. Data collection is anticipated to be complete by late 2017. Outcomes of the trial will be published within a year (12 months) of completing final 12-month follow-up data collection. The study results will be disseminated via conference presentations and papers published in academic peer-reviewed journals. The participants, healthcare professionals, and public will be informed of the study results through email correspondence and local media.

## Discussion

The project has been reviewed and approved by the Tasmanian Health and Medical Research Ethics Committee (H0014568). Prior to enrolling in the study, all participants provide verbal and written consent. Furthermore, additional checks are conducted throughout the study to ensure participant safety in light of details receiving particular attention during the ethical review process. The first is the risk of a negative impact of the receipt (or not) of quit-contingent shopping vouchers on the study participant’s relationship with their partner, with the concern that this may be a potential trigger for family violence or other threat to the safety of the woman (and/or unborn child). During each study visit or telephone call, participants are asked if study participation is impacting negatively on their relationship with their partner. If real or perceived risk is present, the study research officer ensures the safety of the participant by making urgent contact with and referral to the antenatal Social Work service (or after-hours emergency/crisis social work service) at the relevant public hospital to arrange safe accommodation and other services as indicated. The second is the risk of potential distress should a participant experience adverse pregnancy or other outcomes (eg, fetal or infant death) while involved in the study. The research midwife conducts monthly checks of participants’ pregnancy and health status via the Tasmanian Health Service’s digital medical records. In these rare occasions, no further contact is initiated with the participant and her involvement and data is withdrawn. However, should the participant request to continue to participate, she is welcome to do so.

## Appendix

Multimedia Appendix 1 Summary of the time-schedule of visits, rewards, and data collection.

## Abbreviations

AUD: Australian Dollars
CO: Carbon monoxide
DMR: digital medical record
GP: general practitioner
PIQ: Partner Interaction Questionnaire
PIQ-NEG: PIQ negative
PIQ-POS: PIQ positive
ppm: particles per million
